## Methods/Design

### Study design and hypotheses

The study is a randomized longitudinal trial conducted by the Active Aging Resource Center (AARC). AARC is a consortium of university, state, and community partners headquartered at the Center for Health Enhancement Systems Studies at the University of Wisconsin- Madison, WI, USA (CHESS). CHESS develops ICTs to help patients and their families improve their health and well-being. Previous CHESS ICTs have been proven effective in numerous randomized trials for a variety of conditions, including alcohol use disorders [16], lung cancer [17,18], pediatric asthma [19], breast cancer [20], and HIV [21]. CHESS also develops process improvement strategies for healthcare systems.

Participants in the study - older adults and their informal caregivers - are randomized to an intervention group that uses their usual sources of information and communication and has access to Elder Tree from laptops and other devices, or to a control group in which participants use only their usual sources of information and communication. Participants in the Elder Tree group receive access to Elder Tree for 18 months and, if needed, a computer and Internet service. The computer is almost always a touchscreen laptop; two participants have been given large monitors because of vision problems. Participants who have their own desktop, laptop, tablet, or smartphone use their own devices. Participants’ use of other services and interventions is not controlled during the trial in either group.

The primary hypothesis is that older adults assigned to Elder Tree will, compared with a control group, have improved quality of life (QOL). Secondary hypotheses are that older adults assigned to Elder Tree will have, compared with those in the control group, improved independence, lower healthcare costs per Quality-Adjusted Life Year (QALY), less loneliness, fewer falls, improved medication management, and greater ease of transportation and driving, and that informal caregivers with access to Elder Tree will have improved caregiver appraisal (reduced burden, increased mastery of caregiving, and increased satisfaction with the older adult receiving care), and improved coping strategies compared with caregivers without Elder Tree. We also hypothesize that self-determination theory (SDT) will mediate Elder Tree effects.

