**Table 2 Tab2:** **Inclusion and exclusion criteria for randomized clinical trial**

**Older adults**	
Inclusion	• Age 65 or older
criteria	• Live in one of three Wisconsin regions: Milwaukee County; Waukesha County; or Richland, Juneau, or Sauk Counties
	• In the last 12 months, has experienced one or more of the following:
	○ Fallen once or more
	○ Felt sad or depressed
	○ Received home-health services
	○ Stayed in a skilled nursing facility
	○ Gone to the emergency room
	○ Been admitted to the hospital
Exclusion criteria	• Is currently homeless or living in a hospice center, assisted living facility without access to a stove, or nursing home
	• Needs help getting into or out of a bed or a chair

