### Randomization

The project statistician used a computer-generated allocation sequence to randomize eligible older adults (or older adult/caregiver dyads) in a 1:1 ratio to intervention (Elder Tree) or control. Randomization is stratified by geographic region, whether a participant has his or her own computer or other device, and living alone, using random blocks of 4 and 6. Randomization is implemented by the project director using sequentially numbered, sealed, opaque envelopes. The sequence is thus unknown to the county coordinators who enroll participants. Because of the nature of the intervention, neither participants nor research staff are blinded to allocation.

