**Measures related to other challenges**									
**Challenge**	**Construct**	**Instrument**	**Burden**	**When**					**Who**
				**S**	**B**	**6**	**12**	**18**	
Social con-nectedness	Online bonding	CHESS Bonding Scale	4		X	X	X	X	OA
									CG
	Size of social network	# of people to listen to you, to whom you listen, from whom you get help, show love, get together to do something enjoyable	5		X	X	X	X	OA
	Other support	Types of therapy or support groups	6		X	X	X	X	OA
									CG
Service delivery	Satisfaction with service delivery	Showering/bathing/grooming; in-home meal prep or Meals on Wheels; toileting and incontinence; medical support services	4		X	X	X	X	OA
									CG

^a^Hypotheses: compared with the control group, at 6, 12, and 18 months, those randomized to Elder Tree will experience:

1. Improved quality of life (older adults).

2. Improved independence (older adults).

3. Lower healthcare cost per QALY (older adults).

4. Less loneliness (older adults).

5. Fewer falls (older adults).

6. Improved medication management (older adults).

7. Greater ease of transportation and driving (older adults).

8. Improved caregiver appraisal (caregivers).

9. Increased coping strategies (caregivers).

Mediation hypothesis: SDT (autonomy, competence, relatedness) will mediate the effects of Elder Tree on older adult outcomes.

S, screening; B, baseline; OA, older adult; CG, caregiver.

CHESS, Center for Health Enhancement Systems Studies at the University of Wisconsin-Madison, WI, USA; DATCAP, Drug Abuse Treatment Cost Analysis Program; MOS; Medical Outcomes Study; PROMIS, Patient-Reported Outcomes Measurement Information System.

We are also collecting data on the server about how participants use Elder Tree. We use this information to monitor the functioning of the website - for example, see if the website has problems. These use data also will be analyzed after the randomized trial to explore such questions as whether participants who used Elder Tree the most had better outcomes.

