### Data analysis

We will evaluate the effects of Elder Tree by comparing intervention and control participants at 6-, 12-, and 18-month assessments. We will use mixed-effects models to evaluate our primary and secondary hypotheses, where pretest score functions as a covariate, treatment condition is a between-subjects factor, and the multivariate outcome reflects scores for a given assessment across the 3 time points (months 6, 12, and 18). Separate analyses will be conducted for each outcome.

We will use path analysis to test whether the constructs of SDT mediate the relationship between Elder Tree and participants’ QOL at 6, 12, and 18 months. Mediation will be tested based on the significance and size of the specific indirect effects of system use through SDT constructs on relevant outcomes [49-51], as well as the overall fit of the model. Overall model fit will be assessed with statistics traditionally used for this task (for example, CFI, TLI, RMSEA).

Secondary analyses will lend further insight related to primary hypotheses’ findings. The intercorrelations between studied outcomes (for example, Instrumental Activities of Daily Living (IADLs), QOL) and mediator (SDT) will clarify whether these outcomes represent unique versus highly-correlated outcomes. Additional analysis will disaggregate overall Elder Tree effects into component services. Given the non-random selection of services and the potential correlation between the use of certain services, this analysis will address whether a service was used and the intensity of that use. This should reduce multi-collinearity issues in regression analysis and provide insights into each service’s contributions. Outcomes associated with specific Elder Tree services will also be compared between users and non-users of specific services in an exploratory Complier Average Causal Effect (CACE) analysis to examine whether actual use of a service (rather than randomized access to it) is associated with improved outcomes. We will also examine trends within groups over time (for example, whether gains from Elder Tree at 6 and 12 months are maintained to 18 months).

Because we anticipate that Elder Tree will take at least 3 months to have an effect, we plan to conduct exploratory analyses that mirror the aforementioned analyses but exclude participants who die or move to a nursing home or assisted living facility within the first 3 months of the intervention.

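### Whether Elder Tree gains last to month 18 is to be examined through within-group trends, which mix any change in the effect with change common to both arms (minor)

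*Protocol article*

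**What the plan says.** The Data analysis section of the protocol article bases the main evaluation on the randomised comparison: "We will evaluate the effects of Elder Tree by comparing intervention and control participants at 6-, 12-, and 18-month assessments". The model is a mixed-effects model of the three follow-up scores in which "pretest score functions as a covariate, treatment condition is a between-subjects factor". The hypotheses under Table 3 are comparative in the same way: "compared with the control group, at 6, 12, and 18 months, those randomized to Elder Tree will experience" the listed benefits.

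A later paragraph in Data analysis, which covers secondary work, contains the sentence "Secondary analyses will lend further insight related to primary hypotheses’ findings". That paragraph ends with the text at issue: "We will also examine trends within groups over time (for example, whether gains from Elder Tree at 6 and 12 months are maintained" to month 18). No contrast with control is attached to that question.

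Two other places bear on it. Table 2 admits older adults on a recent event: "In the last 12 months, has experienced one or more of the following", namely a fall, sadness or depression, home-health services, a skilled nursing stay, an emergency room visit or a hospital admission. Study design and hypotheses adds: "Participants’ use of other services and interventions is not controlled during the trial in either group".

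**The concern.** By the document's own hypotheses, an Elder Tree gain is a difference from control. Whether it lasts is therefore a question about how that difference changes over time. The sentence hands the question to trends inside each group, and such a trend cannot separate the effect from whatever would have happened to these people anyway.

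A common change is plausible here. Participants enter after a recent adverse event, are 65 or older, are followed for 18 months and may take up other services freely. Recovery would push scores up in both arms and ageing would push them down.

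At stake is a statement about durability, which matters to the payers and community organisations the article hopes to reach. Followed as written, the sentence could support a wrong statement in either direction.

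**Working it through.** **Inputs from the document.** Target N = 450, 225 per group, 80% power, d = 0.3, 80% response (Sample size); allocation "in a 1:1 ratio to intervention (Elder Tree) or control" (Randomization).

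**Inputs assumed.** Two-sided alpha 0.05, SD 1, equal correlation r between visits (0.5 to 0.7), and a time change c common to both arms. The document gives none of these.

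**1. The plan's own figure.** n per arm = 2 × (1.960 + 0.842)² / 0.3² = 174.4, so 175. Allowing for 80% response, 175 / 0.8 = 218.75, so 219 per arm and 438 in total, within 3% of 450. Responders per arm are 225 × 0.8 = 180, at which power is 0.81. The target reproduces, and 180 per arm is used below.

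**2. What a within-arm trend measures.**
- Elder Tree arm: change = change in effect + c
- Control arm: change = c
- Difference between arms: change in effect

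Examples from month 6 to month 18, in SD units:

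| Effect at 6 → 18 | Common change c | Elder Tree arm | Control arm | Difference in change | Elder Tree arm suggests | Truth |
|---|---|---|---|---|---|---|
| 0.3 → 0.3 | −0.3 | −0.3 | −0.3 | 0 | lost | maintained |
| 0.3 → 0 | +0.3 | 0 | +0.3 | −0.3 | maintained | lost |
| 0.3 → 0 | 0 | −0.3 | 0 | −0.3 | lost | lost |
| 0.3 → 0.3 | 0 | 0 | 0 | 0 | maintained | maintained |

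Only when c = 0 does the Elder Tree arm alone give the right answer.

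**3. How often a common change would be flagged when the effect is constant.** SE of the within-arm change between two visits = √(2(1 − r)/180), which is 0.0745 at r = 0.5 and 0.0577 at r = 0.7. Probability of significance = Φ(c/SE − 1.96) + Φ(−c/SE − 1.96).

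| c (SD) | r = 0.5 | r = 0.7 |
|---|---|---|
| 0 | 0.05 | 0.05 |
| 0.1 | 0.27 | 0.41 |
| 0.2 | 0.77 | 0.93 |
| 0.3 | 0.98 | >0.99 |

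**4. Precision of the between-arm alternative.** The contrast is the Elder Tree minus control difference at month 18, less the mean of that difference at months 6 and 12. Per-person variance of Y18 − (Y6 + Y12)/2 = 1 + (1 + r)/2 − 2r = 1.5(1 − r), which is 0.6 at r = 0.6. SE = √(2 × 0.6/180) = 0.082, so a 95% interval has half-width 1.96 × 0.082 = 0.16. Losing half of a 0.3 effect is a change of 0.15, and power to detect it is Φ(0.15/0.082 − 1.96) ≈ 0.45.

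**The case against.** The strongest reply is that the randomised comparison at month 18 is already planned, so the sentence only adds to it. It is one parenthetical example among secondary analyses, with no test or decision rule attached. It speaks of groups in the plural, so the control course will be seen as well, and the modelling detail may sit in a fuller plan.

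Most of this stands and it limits the weight of the point. It does not remove the point. The month-18 comparison shows whether a difference exists then, not whether the earlier difference has changed. The one sentence that addresses maintenance names a method, and that method does not isolate the effect.

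Three stronger readings are tempting, and the document does not support them.
- A reader might infer that the trends measure natural recovery and regression to the mean instead of the Elder Tree effect. The Elder Tree arm's trend contains both the effect and the common change. Regression to the mean should act mainly between baseline and month 6, less over the later interval in question. The document does not quantify it, and decline with age is equally possible.
- A reader might infer that the arms will be compared by whether each reaches significance separately. The article states no such procedure, so error rates for it are not evidence against this plan.
- A reader might infer that the trial's main conclusion is at risk. It is not.

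The alternative has a real weakness too: it is imprecise, as step 4 shows.

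**Conclusion.** The point holds, as a minor one. The stated way of looking at maintenance mixes the change in the Elder Tree effect with change shared by both arms, and can mislead in either direction. The size depends wholly on the common change. With none, the within-arm trend is unbiased for the change in effect. At 0.1 to 0.3 SD, a constant effect would be accompanied by a significant within-arm change with probability 0.27 to 0.98 at r = 0.5, and more often at r = 0.7. These figures illustrate the mechanism under assumed inputs and do not predict what this trial will see. The primary and secondary between-arm comparisons at 6, 12 and 18 months are unaffected.

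**What to change.** Reword the sentence so that maintenance is assessed by a between-arm contrast from the planned mixed model: the Elder Tree minus control difference at month 18 against its mean at months 6 and 12, from the treatment-by-time term, with a confidence interval. Present the within-group curves of both arms as description only, and attribute nothing to Elder Tree from them.

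Add that a non-significant contrast does not demonstrate maintenance, and that the interval should carry the interpretation.

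The cost is a sentence or two of analysis wording. The data and the model are those already planned. The price is precision: a contrast between two arms is noisier than a trend within one, but it answers the question asked.

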### Qualitative data collection and analysis

We have used multiple methods of data collection to plan, develop, and implement Elder Tree, including interviews, surveys, and focus groups with older adults and informal caregivers and testing of the technology as it developed. During the planning phase, we collaborated with the ADRC in each of the three regions participating in the study to identify the assets and challenges of older adults by using a community-based strategy called Asset-Based Community Development [52]. We held meetings with ADRC staff and teams of citizens to develop a plan to interview residents and combine the results. In each area, the three most important challenges identified through the process were identical: isolation and loneliness, how to know about and take advantage of community activities and resources, and transportation. During development, we tested paper prototypes and onscreen iterations of the technology with 335 older adults and caregivers one-on-one and in small groups. During implementation, we continue to digitally collect use data to help us understand and improve the system: for example, use data allow us to see which services in Elder Tree are least used. Knowing this, we can find out why participants are not using a service and how we might improve it. Continuous improvement is a hallmark of our approach to technology as we strive to keep our systems abreast of new or improved operating systems, changing conventions, and other developments.

## Discussion

The development and testing of Elder Tree mark several important advances. Very few technologies have been designed for or rigorously tested with older adults, who often have physical and cognitive limitations not common among younger people. Elder Tree has been developed with the deep involvement of older adults. The technology also has been developed by working closely with community and state partners, such as local Aging and Disability Resource Centers and the Wisconsin Bureau of Aging, both to create a technology that is adaptable to different communities and to build a base for dissemination. Because we will be able to relate outcomes to use of the system, we also hope to understand why and how the system works or does not work and for whom.

Elder Tree is a multifaceted intervention with interacting services. For example, better medication management as a result of using Elder Tree may reduce the risk of falling. These interactions may make it challenging to assess which services or combination of services in Elder Tree account for changes in outcomes. Settling on our recruitment criteria has been an unexpected challenge because our original inclusion criteria proved to be too restrictive.

We have undertaken an active dissemination campaign in Wisconsin from which we hope to learn about effective ways to promote the use of technology among older adults, including those who have not used computers before. By piloting dissemination during the randomized trial phase, we are learning what communities will need to be able to adapt and maintain Elder Tree for their residents and what types of community organizations may want to provide it and why. This early dissemination work will accelerate the transition from research to practice should the randomized trial show positive results.

If Elder Tree can improve the quality of life of older adults and reduce healthcare costs, it could suggest one path to significantly reducing the physical, emotional, and financial burdens that advancing age can place on older adults, their families and communities, and the healthcare system.

## Trial status

The trial has received ethical approval and recruited 392 participants to date (31 March 2015). We anticipate ending recruitment in May 2015.

## Abbreviations

AARC: Active Aging Resource Center
ADLs: Activities of Daily Living
ADRC: Aging and Disability Resource Center
CACE: Complier Average Causal Effect
CHESS: Center for Health Enhancement Systems Studies at the University of Wisconsin-Madison, WI, USA
DATCAP: Drug Abuse Treatment Cost Analysis Program
IADLs: Instrumental Activities of Daily Living
ICERs: Incremental cost-effectiveness ratios
ICT: Information and communication technology
IT: Information technology
PROMIS: Patient-Reported Outcomes Measurement Information System
QALY: Quality-Adjusted Life Year
QOL: Quality of life
REDCap: Research Electronic Data Capture
SDT: Self-determination theory
SPIRIT: Standard Protocol Items: Recommendations for Interventional Trials
WHO: World Health Organization
